## Abstract

**Background:**

Patients with early stage papillary thyroid carcinoma (PTC), are faced with the decision to either to accept or reject adjuvant radioactive iodine (RAI) treatment after thryroidectomy. This decision is often difficult because of conflicting reports of RAI treatment benefit and medical evidence uncertainty due to the lack of long-term randomized controlled trials.

**Methods:**

We report the protocol for a parallel, 2-arm, randomized trial comparing an intervention group exposed to a computerized decision aid (DA) relative to a control group receiving usual care. The DA explains the options of adjuvant radioactive iodine or no adjuvant radioactive iodine, as well as associated potential benefits, risks, and follow-up implications. Potentially eligible adult PTC patient participants will include: English-speaking individuals who have had recent thyroidectomy, and whose primary tumor was 1 to 4 cm in diameter, with no known metastases to lymph nodes or distant sites, with no other worrisome features, and who have not received RAI treatment for thyroid cancer. We will measure the effect of the DA on the following patient outcomes: a) knowledge about PTC and RAI treatment, b) decisional conflict, c) decisional regret, d) client satisfaction with information received about RAI treatment, and e) the final decision to accept or reject adjuvant RAI treatment and rationale.

**Discussion:**

This trial will provide evidence of feasibility and efficacy of the use of a computerized DA in explaining complex issues relating to decision making about adjuvant RAI treatment in early stage PTC.

**Trial registration:**

Clinical Trials.gov Identifier: NCT01083550

## Background

Thyroid cancer is increasingly being diagnosed in North America and Europe [1-5]. Papillary thyroid carcinoma (PTC) accounts for the majority of these newly diagnosed cases [1,6]. Most patients diagnosed with PTC have early stage disease and are at low risk of dying from thyroid cancer [7]. It is currently recommended that most patients with PTC undergo surgical removal of the thyroid (total or near-total thyroidectomy), to be followed by life-long thyroid hormone therapy [8-10]. Adjuvant radioactive iodine (RAI) treatment or the option of no adjuvant RAI treatment (with close medical follow-up) may be offered in early stage PTC after thyroidectomy [8,11]. There are no long-term randomized controlled trials examining whether adjuvant RAI treatment reduces the risk of thyroid cancer-related recurrence or mortality in early stage PTC, and the best available observational evidence includes conflicting reports of treatment benefit [11]. The potential risks, benefits, reproductive considerations, and implications for disease follow-up must be considered in RAI decision making. However, in early stage PTC, adjuvant RAI treatment decision-making is complex and subject to some uncertainty [11].

In a recent focus group study conducted in Canada [12], thyroid cancer survivors reported receiving conflicting recommendations on adjuvant post-surgical RAI treatment from healthcare providers and insufficient information on rationale, risks, and uncertainties relating to this treatment. In many cases, no choice was offered and patients felt the treatment was imposed on them. This lack of clarity in communication has led thyroid cancer survivors to call for the development of plain-language, evidence-based information on this topic, such as in a DA [12]. Decision aids are instruments used to inform patients about available treatment options which have been found to generally improve general patient knowledge, to result in more realistic patient treatment expectations, to increase active patient participation in decision making, and to reduce indecisiveness, when compared to usual care; DA's may be computerized or paper-based or a combination of both [13].

Our aim in this randomized controlled trial, is to evaluate, in individuals with early stage PTC who have had thyroidectomy, the effect of a computer-based DA on the following outcomes: a) knowledge about PTC and RAI treatment (primary outcome), b) decisional conflict, c) decisional regret, d) client satisfaction with information received about RAI treatment, and e) the final decision to accept or reject adjuvant RAI treatment and the rationale for this decision. The comparator group will be individuals with early stage PTC who have not been exposed to the DA but who have received usual care from their physicians. We present herein the protocol that we are using to conduct this trial.

## Methods

### Design

In order to evaluate this DA, we propose to conduct a single-centre, patient-level randomized controlled trial, comparing exposure to the DA (with usual care) to a control group of usual care. The study protocol has been approved by the University Health Network Research Ethics Board. Signed informed consent will be obtained from all participants.

### Setting

Administration and testing of the DA will be conducted in a research office at the Toronto General Hospital site of the University Health Network in Toronto, Canada. The University Health Network is a tertiary care referral centre for thyroid cancer care. Participants not cared for at the University Health Network will be eligible for participation in the trial, providing the report of their thyroid surgical pathology may be reviewed by investigators, to ascertain eligibility.

### Participants

#### Inclusion criteria

Participants in the study will include individuals with early stage papillary carcinoma in whom either accepting or rejecting adjuvant RAI treatment are reasonable, given the lack of clear-cut evidence guiding therapy. Potentially eligible patient participants will include: individuals who have had complete resection of their thyroid at surgery (total or near-total thyroidectomy, or hemi- [subtotal] with completion thyroidectomy) at the age of 18 years or older, in the time since September 1, 2009 (last thyroid surgery on or after September 1, 2009). The papillary thyroid cancer must have been of TNM pathologic stage pT1 or pT2, N0 (or Nx), M0 (or Mx) (TNM stage, American Joint Committee on Cancer VI [14]) (ie. primary tumor size 1-4 cm, no known positive lymph nodes at the time of primary surgery, no extension of the tumor outside the thyroid, no venous or lymphatic invasion, and no known distant metastases at primary surgery, with no tall cell features, as per surgical pathology report). Individuals concurrently diagnosed with medullary or anaplastic or poorly differentiated thyroid cancer or thyroid lymphoma are not eligible for the study. Participants must be able to communicate in spoken and written English and able to use a computer and provide informed consent on their own (without any need for translation). The reason for the English language fluency criterion is that the DA is currently available only in English.

#### Exclusion criteria

Individuals who have already received RAI treatment for thyroid cancer are not eligible for this study, since the decision to accept RAI treatment would have already been made in such individuals. However, individuals meeting inclusion criteria who are on the waiting list for RAI treatment may be eligible, since their decision could still be subject to change. Participants not meeting the inclusion criteria will be ineligible. Individuals who have been temporarily stopped taking thyroid hormone (for the purpose for testing or RAI treatment), will not be eligible for the study while off this medication, since it could potentially impact cognitive ability. Individuals who are unwilling for investigators to confirm their pathologic stage of thyroid cancer through review of pathology reports, will be ineligible for the study.

#### Participant recruitment

Participants will be recruited through the following means: a) review of recent pathology records reviewed at University Health Network, with mailing of information about the study to potentially eligible participants, b) review of the radioactive iodine treatment wait list at the University Health Network, with mailing of the information about the study to potentially eligible participants, c) use of posters and flyers about the study in University Health Network (hallways, patient wait areas, and clinics), d) dissemination of information about the study through internet media and possibly newsletters of a Canadian thyroid cancer support group (Thyroid Cancer Canada, formerly known as Thry'vors), e) and distribution of information about the study via e-mail (and pamphlets, if requested) to thyroid cancer physicians in the Greater Toronto Area. Recruitment materials will indicate that potentially interested participants should telephone the research office for more information. A research staff member will then inform potential participants about the trial and collect information on eligibility. All pathology reports of potential participants will be reviewed for eligibility by either the primary investigator ([name]) or co-investigator ([name]). A consent form for release of medical information will be signed by potentially eligible participants to obtain thyroid cancer surgical pathology reports from treating physicians, if this information is not already available to investigators nor provided by patients at recruitment. Patient participants will be compensated with $100 after completion of the first study visit (randomization and testing) and with an additional $100 for completion of the telephone follow-up.

### Intervention

#### Decision aid

A multi-disciplinary team of thyroid cancer physicians and methodologists were involved in development of the computerized DA. The content of the DA was based on the information needs identified by thyroid cancer survivors in a focus group study [12] and the physician members involved in development. Multiple systematic reviews of the literature were conducted in order to ensure the DA content was evidence-based [11,15-17]. The DA was subjected to pre-testing by thyroid cancer physicians, thyroid cancer survivors, and lay individuals (usability testing followed by revisions).

For participants randomized to the intervention group, the DA website will be opened for the participant by staff and the participant will be asked to self-navigate the website. The number of computer mouse clicks used to retrieve information and the duration of DA examination will be recorded for each participant in the intervention group. It will be suggested to the participant that he or she may spend up to 60 minutes reviewing the website, but he or she may finish early if desired. The participant will review the information in the DA on his or her own during one visit at the Toronto General Hospital, with no access to the website nor print-outs allowed at home. A research assistant will be present in the same room during the study visit, in case the participant has any questions about navigation of the DA. All participants in the intervention group will receive usual care from their treating physicians.

### Usual care control group

The usual care control group will be provided counselling and care from their own treating physicians, and not provided any exposure to the DA during the trial.

### Randomization

Central computerized randomization will be performed in a 1:1 ratio (variable block sizes) at a patient participant level. The randomization will be to the intervention group (exposure to the computerized DA in addition to usual care) or control group (no exposure to the DA, only usual care). The randomization will be achieved through the DA program, after the study staff enters the participant's unique identifier number, to be immediately followed by testing. Allocation will be concealed until the this testing visit. Thus, prior to the testing visit, neither the participant, study staff, investigators, nor treating physicians will be aware of the allocation.

### Outcomes, follow-up, and data collection

Participant involvement in the trial will include one visit to the Toronto General Hospital, at which point, signed informed consent for participation in the trial will be obtained, and baseline data will be collected on demographic characteristics and psychological coping style [18]). The randomization will be performed, and the intervention administered at this time (for those randomized to the DA group), and self-administered questionnaires will be completed. A telephone follow-up interview will be performed at 6 months (with telephone follow-up in subsequent months, after the decision on RAI treatment has been finalized).

To assess efficacy of the DA intervention, the primary outcome measured in this trial will be the score (number of correct responses out of 10 questions) on a self-administered written questionnaire examining knowledge about PTC and RAI treatment, which will be administered at the randomization visit (immediately after exposure to the DA in the intervention group, or after revealing no exposure to the DA in the control group). After the knowledge questionnaire is completed, decisional conflict [19,20] relating to the decision to accept or reject adjuvant RAI treatment will be assessed as a secondary outcome, using a self-administered questionnaire in all participants.

### Statistical considerations

#### Quantitative analysis

For descriptive analyses, categorical data will be expressed as number and proportion (or percentage), whereas continuous data will be expressed as mean and standard deviation (or median and range). Independent sample t-tests will be used to compare questionnaire scores, using an intention-to-treat principle. A chi-squared analysis will be used to compare the proportion of individuals accepting RAI treatment in the intervention group compared to the control group (separate analyses for all participants, as well as excluding those on the radioactive iodine treatment wait list at the time of recruitment). Alpha = 0.05 will be used as the cut-off for statistical significance for all analyses. Missing data for any questionnaire subscales will be imputed from the mean of the rest of the questions within that subscale, for questionnaires in which subscales are established.

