#### Sample size calculations

The sample size is calculated to detect a one point difference in the mean score of the knowledge questionnaire (relating to PTC and RAI treatment), between the intervention and usual care groups, assuming a standard deviation of 1.5 (Power and Precision software, Biostat, Inc., Englewood, NJ, USA). The intended sample size is 37 individuals per group (total of 74) (0.05 2-tailed alpha, power 0.808).

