### Additional exploratory analyses

We will examine the following Spearman correlation coefficients for the baseline monitoring and blunting coping questionnaires scores (as measured by the MBSS) relative to the following: a) number of computer mouse clicks used by individuals in the intervention group to retrieve information within the DA, b) knowledge questionnaire score, c) and participant satisfaction with information received, as assessed at telephone follow-up. We will also compare the MBSS scores in individuals who ultimately receive adjuvant RAI treatment compared to those who reject it (Student's t-tests).

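### The primary knowledge score is compared by a valid, correctly powered but unadjusted t-test; adjusting for one or two baseline covariates already collected could add precision at low cost

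*Protocol article*

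**What the plan says.** The primary endpoint is defined under Outcomes, follow-up, and data collection: "the primary outcome measured in this trial will be the score (number of correct responses out of 10 questions". It is measured once, at the randomisation visit, after the decision aid has been viewed or after the participant learns that it will not be shown. No knowledge test before the intervention is described.

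The method is fixed under Quantitative analysis: "Independent sample t-tests will be used to compare questionnaire scores, using an intention-to-treat principle". The sentence covers all questionnaire scores, the primary one included.

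The same visit also yields other information. In the Outcomes section "baseline data will be collected on demographic characteristics and psychological coping style", and this is listed ahead of randomisation. The individual demographic items are not named. Coping style reappears only under Additional exploratory analyses: "We will examine the following Spearman correlation coefficients for the baseline monitoring and blunting coping questionnaires scores", one of the correlates being the knowledge score.

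The sample size section is built on the unadjusted comparison: "The sample size is calculated to detect a one point difference in the mean score of the knowledge questionnaire", "assuming a standard deviation of 1.5", leading to "The intended sample size is 37 individuals per group (total of 74) (0.05 2-tailed alpha, power 0.808". The Randomization section names variable block sizes and no stratification factor.

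**The concern.** In a two-arm trial with a continuous outcome, adjusting for a baseline variable that predicts the outcome reduces the residual variance and leaves the target unchanged: in a linear model it is still the difference in mean score between arms. The planned analysis takes no such advantage. With no stratification and no baseline knowledge score, demographics and coping style are the main pre-allocation variables that the article says it collects and that could do this work. Age or education (if recorded) could plausibly bear on a written knowledge test, and the investigators themselves think the relation between coping style and knowledge worth examining.

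What is at stake is efficiency: a somewhat narrower confidence interval and somewhat higher power from the same 74 participants. Prespecifying the set has a second use, since it rules out choosing covariates after seeing which characteristics happen to differ between two groups of 37.

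**Working it through.** **Inputs.** From Sample size calculations: difference 1 point, SD 1.5, n = 37 per group, two-sided alpha 0.05, stated power 0.808. From Randomization: 1:1 allocation. Assumed here, because the article gives no value: R2, the share of within-arm variance in the knowledge score explained by the covariates.

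**Step 1: reproduce the stated power.**
- Standard error = 1.5 × √(2/37) = 0.3487.
- Noncentrality = 1/0.3487 = 2.867, with 72 degrees of freedom and critical value 1.993.
- Power from the noncentral t distribution = 0.8076, against 0.808 stated. At 36 per group it is 0.797.

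Test, sample size and power agree with one another.

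**Step 2: adjusted analysis with k covariates.** Adjustment multiplies the variance by (1 − R2). Estimating k coefficients leaves 72 − k degrees of freedom and, through chance covariate imbalance, multiplies the variance by about 1 + k/(71 − k). So:

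effective SD = 1.5 × √[(1 − R2) × (1 + k/(71 − k))]

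For k = 2 the inflation factor is 1 + 2/69 = 1.029, with 70 degrees of freedom and critical value 1.994.

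| R2 (assumed) | Effective SD | Standard error | Noncentrality | Power |
|---|---|---|---|---|
| 0 | 1.5216 | 0.3538 | 2.827 | 0.796 |
| 0.03 | 1.4986 | 0.3484 | 2.870 | 0.808 |
| 0.05 | 1.4831 | 0.3448 | 2.900 | 0.816 |
| 0.10 | 1.4435 | 0.3356 | 2.980 | 0.836 |
| 0.20 | 1.3609 | 0.3164 | 3.160 | 0.876 |

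The break-even point is roughly where (1 − R2) × 1.029 = 1, that is R2 = 2/71 = 2.8%. Solving exactly, with the lost degrees of freedom included, gives 2.9%, a multiple correlation of √0.029 = 0.17.

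**Step 3: number of covariates.** Same formula:

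| Covariates | Power, R2 = 0 | R2 = 0.10 | R2 = 0.20 | Break-even R2 |
|---|---|---|---|---|
| 1 | 0.802 | 0.841 | 0.881 | 1.4% |
| 2 | 0.796 | 0.836 | 0.876 | 2.9% |
| 3 | 0.790 | 0.831 | 0.872 | 4.3% |
| 4 | 0.784 | 0.825 | 0.867 | 5.8% |

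Each extra covariate costs about 0.6 points of power unless it raises R2. A multi-level factor counts once per level beyond the first. This favours a short list.

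**Step 4: does adjustment protect against a larger SD?** Only modestly. If the SD were 2.0 (an assumption), the t-test would have power 0.564. Two covariates with R2 of 0.10 give an effective SD of 2 × √(0.9 × 1.029) = 1.925, a noncentrality of 2.235 and power of 0.596.

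**The case against.** The strongest reply is that nothing here is wrong. The t-test is valid under 1:1 randomisation, matches the sample size calculation and has a conventional power, correctly computed. No stratification factor is named, so the analysis omits none. A fuller analysis plan, not shown, may add an adjusted model. All of this stands, and it makes the point an improvement rather than a correction. The point survives because the article does state its test for the primary outcome, and a better use of data already held is available.

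A reader might infer more than the document supports, in four ways:

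- *That the baseline data are known to predict knowledge.* They are not. The coping correlations are an exploratory question with no direction or size predicted, education is not named as collected, and the likely strongest covariate, a prior knowledge score, does not exist.
- *That the gain is free.* It is not: power falls slightly below that of the t-test if the covariates explain almost nothing.
- *That power of 0.808 is a weakness.* It is an ordinary level. A larger SD than assumed would be a problem of the SD assumption, and adjustment with a modest R2 would hardly repair it.
- *That chance imbalance undermines the t-test.* It does not. The standard error and type I error already allow for it under randomisation; adjustment affects precision, not validity.

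**Conclusion.** The point holds as a low-cost gain in efficiency, not as an error or contradiction. With two covariates, the expected change in power runs from a loss of about one point (0.808 to 0.796) if they explain nothing, to a gain of about three points at an R2 of 10% and about seven at 20%. The break-even R2 is about 3%, which is a low bar, but the document offers no evidence on whether it is met.

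These figures rest on the article's SD of 1.5 and difference of 1 point, on assumed R2 values, on a linear covariate effect, and on covariates that are recorded before allocation. The sample size of 74 needs no change.

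**What to change.** Under Quantitative analysis, before any analysis of outcome data, state that the primary comparison is a linear model of knowledge score on arm plus one or two named pre-randomisation covariates already collected. Examples are the MBSS monitoring score, and age or education if these are among the recorded demographics. Choose them on subject-matter grounds, enter each in a form that uses one degree of freedom where possible, and do not select them on observed imbalance or on their correlation with the outcome in this trial. Report the adjusted mean difference with its 95% CI. Keep the independent-samples t-test as a supportive analysis, which also preserves the link to the sample size calculation.

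The cost is a sentence or two in the analysis section, up to two degrees of freedom, and at worst about one point of power. No additional patients or data are needed. No power target is stated for decisional conflict, satisfaction or regret, so using the same model there is optional.

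### The all-participants comparison of RAI choice is valid but unadjusted for wait-list status, a baseline variable the trial already records; a wait-list-stratified test would use the same 74 patients more efficiently if that status is strongly prognostic

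*Protocol article*

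**What the plan says.** Under Quantitative analysis, the protocol article states: "A chi-squared analysis will be used to compare the proportion of individuals accepting RAI treatment in the intervention group compared to the control group". The test is run in two populations: "separate analyses for all participants, as well as excluding those on the radioactive iodine treatment wait list at the time of recruitment". The same section sets the threshold: "Alpha = 0.05 will be used as the cut-off for statistical significance for all analyses". No covariate or stratum is named for this comparison.

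Wait-listed patients are admitted on purpose. Exclusion criteria allows those "who are on the waiting list for RAI treatment may be eligible, since their decision could still be subject to change", and Participant recruitment lists "review of the radioactive iodine treatment wait list at the University Health Network" among the recruitment routes. Under Randomization, "Central computerized randomization will be performed in a 1:1 ratio (variable block sizes) at a patient participant level"; no stratification factor is stated.

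The final RAI decision is the last of five outcomes listed in the Background; knowledge is primary. Sample size calculations rests on the knowledge score alone: "The intended sample size is 37 individuals per group (total of 74) (0.05 2-tailed alpha, power 0.808"). The article gives no wait-list share, RAI uptake rate or power for RAI choice.

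**The concern.** A patient on the RAI wait list has at least provisionally agreed to treatment. The article itself treats this as relevant to the outcome: it justifies admitting these patients by saying their decision may still change, and it plans an analysis without them. Wait-list status is therefore a plausible strong predictor of the final decision. It is fixed before randomization and costs nothing extra to collect.

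The plan uses it only to remove patients in the second analysis. The first analysis keeps everyone but leaves the variation in uptake between wait-listed and other patients in the error term. With 37 per arm, that can cost a useful share of the power to see an effect of the decision aid on treatment choice, one of the trial's named outcomes.

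**Working it through.** **1. The article's own figure.** Inputs from Sample size calculations: difference 1 point, SD 1.5, 37 per group, two-sided 0.05. The noncentrality is 1 / (1.5 × √(2/37)) = 2.867 with 72 df, and the noncentral t gives power 0.8076. The stated 0.808 reproduces. It concerns knowledge only.

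**2. Assumptions for RAI choice.** The article supplies none of the following, so all are assumed: wait-list share 30% or 50% of 74 (22 or 37 patients); control uptake 90% if wait-listed and 30% if not; various reductions under the decision aid.

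**3. Validity of the crude test.** With half wait-listed and no true effect, the crude chi-squared test rejects in about 4.6% of simulated trials. Chance imbalance is already part of its sampling variability:
- The probability that the arms differ by 5 or more wait-listed patients is 0.353 (hypergeometric: 37 drawn from 74, of whom 37 are wait-listed).
- A 5-patient gap shifts the expected difference by 5/37 × (0.90 − 0.30) = 8.1 points, about 0.7 of the crude SE in step 4. With that gap fixed (21 vs 16), the crude test still rejects in about 5.1% of null trials.
- A larger gap, 18 vs 12 with 30 wait-listed, shifts it by 6/37 × 0.60 = 9.7 points, and conditional rejection rises to about 0.08.

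**4. Precision, half wait-listed.** Overall control uptake is 0.5 × 0.90 + 0.5 × 0.30 = 0.60.
- Crude SE: √(2 × 0.60 × 0.40 / 37) = 0.114.
- Stratified SE: √(2 × (0.5 × 0.90 × 0.10 + 0.5 × 0.30 × 0.70) / 37) = √(2 × 0.15 / 37) = 0.090.
- Variance ratio: 0.15 / 0.24 = 0.625, a reduction of about 37%.

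**5. Power by simulation** (37 per arm, two-sided 0.05). WL = wait-listed; CMH = Cochran-Mantel-Haenszel stratified by wait-list status.

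| Scenario | Crude, all | Excluding WL | CMH, all |
|---|---|---|---|
| 50% WL; 90%→65% and 30%→5% | 0.58 | 0.55 | 0.80 |
| 30% WL; 90%→65% and 30%→10% | 0.47 | 0.46 | 0.64 |
| 50% WL; 90%→80% and 30%→20% | 0.13 | 0.11 | 0.19 |
| 50% WL; 85%→75% and 40%→30% | 0.13 | 0.10 | 0.16 |
| 50% WL, barely prognostic; 60%→35% and 50%→25% | 0.58 | 0.35 | 0.59 |
| 50% WL; effect only if not WL: 90% unchanged, 30%→5% | 0.18 | 0.55 | 0.34 |
| 50% WL; effect only if not WL: 90% unchanged, 50%→25% | 0.19 | 0.35 | 0.26 |

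A wider grid (20% to 60% wait-listed; control uptake 90–95% vs 20–50%; common odds ratio 1/3 or 1/4) gives CMH a gain over the crude test of about 6 to 22 points.

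Stratifying beats or matches the crude all-participants test in every row. It does not beat the exclusion analysis when the effect is confined to patients not on the wait list.

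**The case against.** The strongest case for the plan is that nothing in it is invalid. An unadjusted chi-squared test in a randomized trial holds its error rate, and the exclusion analysis selects on a pre-randomization characteristic, so its comparison remains randomized. This stands, and it rules out some tempting stronger readings:

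- A reader might infer that chance imbalance in wait-listed patients biases the RAI-choice result. It does not do so systematically: even a fixed 5-patient gap leaves the error rate near nominal, and only a rarer, larger gap raises it noticeably.
- A reader might infer that the plan ignores wait-list status and then throws these patients away. The wording does not support this: the exclusion analysis is additional to the analysis of everyone.
- A reader might infer that one stratified test should replace both planned tests. It should not: wait-listed patients may respond less, and if they do not respond at all, the exclusion analysis is the most powerful of the three.
- A reader might extend the point to decisional conflict. The article gives nothing from which to size such a gain, and its t-test is valid.

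It is also fair that the gain depends on rates the article does not give, that the largest gain needs a large effect in both groups, and that the outcome is not primary and carries no power claim. Ranking secondary analyses is often left to an analysis plan that is not shown, so the absence of a ranking is not itself a fault. What survives is narrower: the article does fix the test for the all-participants comparison, and a better one is available from data the trial already collects.

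**Conclusion.** The point holds as one of efficiency. The crude all-participants test is valid but wasteful if wait-list status strongly predicts the decision. Under assumed control uptake of 90% vs 30%, 30% to 50% wait-listed, and reductions of 20 to 25 points in both groups, stratifying adds about 17 to 22 points of power (0.47 to 0.64, and 0.58 to 0.80). With a 10-point reduction the gain is about 6 points and neither test has useful power. If status is barely prognostic there is no gain and no loss. That wait-list status is strongly prognostic is plausible from the article's own reasoning but is not shown by any figure in it. The primary analysis and the sample size are unaffected.

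**What to change.** In Quantitative analysis, replace the crude chi-squared test in all participants by a Cochran-Mantel-Haenszel test, or a logistic model with wait-list status as a covariate, in all randomized participants, using wait-list status at recruitment. Name it the main RAI-choice analysis and report the stratified risk difference with a 95% CI. Keep the planned analysis without wait-listed patients as a pre-specified supportive analysis, and report results by stratum so that an effect confined to one group is visible. Make the change before outcomes by arm are seen.

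The cost is a wording change and one extra analysis step; no new data or patients are needed. Stratifying the central randomization by wait-list status, and adjusting decisional conflict for it, are optional.
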